### Blinding

The researcher who will conduct the assessments will be blinded to the group assignment and study objectives and will not participate in the intervention protocols.

The participants will be blinded to the intervention. For such, all electrode placement procedures will also be performed in the sham group; the stimulator will be switched on for only 30 s and then switched off. Thus, the subjects in the sham group will have the initial sensation of electrostimulation but will not receive any stimulus during the remaining time. The participants will be blinded to the modality of application of the active tDCS intervention or sham tDCS. However, the blinding will be unlocked to the guardian/participant if there is inconsistency in possible adverse effects and/or questioning on the part of the guardian. If this unblocking occurs, the individuals will be able to finish the protocol but will not compose the results of the study.

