**Methods/design:**

Two investigations are proposed: (1) an observational study with a convenience sample consisting of children with Down syndrome (group 1—cognitive age of 6 to 12 years according to the Wechsler Abbreviated Scale of Intelligence) and children with typical development 6 to 12 years of age (group 2). Both groups will undergo evaluations on a single day involving a three-dimensional analysis of upper limb movements, an analysis of muscle activity of the biceps and brachial triceps muscles and an analysis of visuospatial and cognitive-motor variables. (2) Analysis of clinical intervention: a pilot study and clinical trial will be conducted involving individuals with Down syndrome (cognitive age of 6 to 12 years according to the Wechsler Abbreviated Scale of Intelligence). The sample will be defined after conducting a pilot study with the same methodology as that to be used in the main study. The participants will be randomly allocated to two groups: An experimental group submitted to anodal tDCS combined with a VR game and a manual motor task and a control group submitted to sham tDCS combined with a VR game and a manual motor task. The training protocol will involve 10 sessions of active or sham tDCS during memory and motor task games. Three 20-min sessions will be held per week for a total of 10 sessions. Evaluations will be performed on three different occasions: pre-intervention, post-intervention (after 10 sessions) and follow-up (1 month after the intervention). Evaluations will consist of analyses of electroencephalographic signals, electromyographic signals of the biceps and triceps brachii, and the three-dimensional reconstruction of the reaching movement. The results will be analyzed statistically with the significance level set at 5% (*p* ≤ 0.05).

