### Ethical aspects

The present study complies with the norms governing research involving human subjects stipulated by the Brazilian National Board of Health in October 1996 and updated in Resolution 466 in 2012 as well as the precepts delineated in the Declaration of Helsinki. The study received approval from the Research Ethics Committee of the School of Medical Sciences of the Santa Casa de São Paulo (certificate number: 3.608.521) and was registered with the Brazilian Registry of Clinical Trials (REBEC protocol number RBR-43pk59 registered on 2019/03/27). The authors confirm that all ongoing and related trials for this intervention are registered. All participants and their legal guardians will agree to participate in the study by signing a statement of informed consent (Appendix A) and Minor Consent Form (Appendix B). The consent form is available in the local language. The participants and their guardians will have the opportunity to ask questions about participation in the study. Once a participant and guardian agree to participate, the study team will obtain written consent. Written permission will be obtained from the legal guardians and consent to participate will be obtained from the participants.

The participants will be allowed to abandon the study at any time with no negative consequences. Absolute confidentiality regarding the identification of children will be assured. The participants will be informed of the existence of a sham group prior to the start of the survey. The sham intervention procedures will always be performed in combination with active (VR training), reducing the impact on the patient. No biological material will be collected. The participants will provide consent separately for the use of images but will be assured that their identity will be maintained confidential in all stages of the study.

In studies 2 and 3, the participants will receive an intervention scheme with active or sham tDCS. Depending on the results, a protocol will be used at the end of the study so that everyone receives the active intervention to ensure that all participants benefit during the study.

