### Data management and monitoring

Data on the participants will be collected during the eligibility assessment. Signed consent forms will be safeguarded. This study will be performed in accordance with the approved protocol. If a participant is excluded or withdraws from the study, the reason for the exclusion will be recorded.

Due to the simplicity and safety of the protocol, we do not expect the participants to experience any adverse events. If the participant presents any side effect related to the intervention process, such as itching, burning sensation, headache, or pain, the event will be reported to the ethics committee and procedures will be performed to ensure the participant's safety. Adverse events will be carefully monitored during this study. The team at the clinical intervention sites will monitor and report all minor and serious adverse events that occur, if any, from enrollment to the end of the study. The researchers will also make telephone calls one day after each session of the intervention for clinical follow-up of the participant.

Descriptive data will be recorded using electronic anthropometric forms and registration forms that will be filled out and sent to the data analyst of the Human Movement Analysis laboratory at Universidade Evangélica, Goiás, Brazil. The data will be entered into a study-specific database by trained staff. The study will be carried out by a multidisciplinary team linked to the Movement Analysis Laboratory of the University Evangelica, Goias, Brazil, composed of clinical researchers, the School of Medical Sciences of São Paulo, São Paulo, Brazil, the Politecnico di Milano, Milano, Italy, and the Strathclyde University, Glasgow, Scotland.

The researchers will have weekly calls to track the progress of the study and ensure adherence to the design, schedule, and budget.

An endpoint adjudication committee led by [name] will meet to review, have access to these interim results and make the final decision to terminate the study.

The Data Security and Monitoring Board is independent and consists of a statistician, clinical researchers, health science specialists, data engineering specialist, and specialists in the use of tDCS and VR.

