#### Adverse effects

Potential adverse effects of tDCS will be assessed at the end of each session using a questionnaire administered to the child. The questionnaire will address the perception of symptoms that occurred during the session, such as tingling, itching, burning sensation, headache, pain at the electrode site, drowsiness, and altered mood. The participants will be instructed to respond using a three-point scale. Caregivers and children will also receive open-ended questions at the beginning of each session addressing the occurrence of headache, scalp pain, itching, burning sensation, redness of the skin, drowsiness, difficulty concentrating, and mood swings between sessions.

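### A guardian's question alone can reveal the allocation and, by the next sentence, remove the child from the results, so families can trigger a post-randomisation exclusion

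*Protocol article*

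**What the plan says.** The Blinding section sets the intention: "The participants will be blinded to the modality of application of the active tDCS intervention or sham tDCS". It then makes an exception, under which "the blinding will be unlocked to the guardian/participant if there is inconsistency in possible adverse effects and/or questioning on the part of the guardian". It goes on to say that after such a disclosure "the individuals will be able to finish the protocol but will not compose the results of the study".

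Three other places bear on how often the exception could be used.

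- Ethical aspects: "The participants will be informed of the existence of a sham group prior to the start of the survey".
- Adverse effects: "Caregivers and children will also receive open-ended questions at the beginning of each session".
- Data management and monitoring: "The researchers will also make telephone calls one day after each session of the intervention".

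The course is ten sessions (abstract, Methods/design; repeated under Intervention protocol). Under Group allocation, the treating therapist opens the allocation envelope, and all outcomes are measured by blinded assessors. Under Recruitment, Study 2, the calculated sample size is raised by 20% for dropout.

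**The concern.** The exception has two triggers joined by and/or, so either is sufficient. The second is that the guardian asks. No safety need, severity threshold or independent decision-maker is attached to it.

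Two things then follow from one question. The sham blind is broken for that family, and the child leaves the results after randomisation. If such exclusions occurred equally and for the same reasons in both arms, they would cost only precision. They need not. A guardian may ask because the child felt a lot, or nothing, or seems not to be improving, and each of these can differ between active and sham stimulation. The children left in the results would then no longer be the groups that were randomised. The exclusions also draw on the same 20% allowance that is meant to cover ordinary dropout.

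**Working it through.** The article states no unblinding rate and no phase 3 sample size, so there is no plan figure to reproduce. What can be checked is the number of planned contacts and what an assumed rate would imply.

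**Contacts.** Ten sessions, each with one enquiry to the caregiver at the start and one call the next day: 10 × (1 + 1) = 20. The two familiarisation sessions (Virtual reality), the evaluation visits and the reminder messages come on top, so 20 is on the low side. Counting the calls alone gives 10.

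**Share unblinded and excluded.** Let p be the assumed chance that a guardian questions the allocation at any one contact, and c the number of contacts. With independent, equal chances, the share is 1 − (1 − p)^c. For c = 20: 1 − 0.995^20 = 0.095, 1 − 0.99^20 = 0.182, 1 − 0.98^20 = 0.332.

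| p (assumed) | 10 contacts | 20 contacts | 30 contacts |
|---|---|---|---|
| 0.5% | 4.9% | 9.5% | 14.0% |
| 1% | 9.6% | 18.2% | 26.0% |
| 2% | 18.3% | 33.2% | 45.5% |

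**The dropout allowance.** Raising n to 1.2n tolerates a loss of 1 − 1/1.2 = 16.7%. Setting 1 − (1 − p)^20 = 1/6 gives p = 1 − (5/6)^(1/20) = 0.9%. At that rate per contact, the whole allowance is gone before any ordinary dropout. The corresponding p is 1.8% for 10 contacts and 0.6% for 30.

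**Power, as an illustration.** Assume a standardised effect of 0.5, with the article's one-sided 5% level and 80% power. This needs 50 per arm, or 60 after the increase. With 18.2% excluded, 60 × 0.818 = 49.1 per arm remain and power is 79.7%. With 33.2% excluded, 60 × 0.668 = 40.1 remain and power is 72.4%. Both figures assume no other loss.

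**The pilot.** It has ten children and uses the main study's methods, so the clause applies there too. The chance that at least one of the ten is unblinded and excluded is 1 − (1 − p)^200, which is 63% at p = 0.5% and 87% at p = 1%. This is the sample from which the phase 3 size is to be calculated.

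**The case against.** A reader might infer that children who know their arm enter the active-versus-sham comparison, so that changed effort in the reaching task or changed self-report of adverse effects biases the result directly. The article does not support this. Its next sentence takes unblinded children out of the results, so knowledge of the arm cannot shift the reported contrast through their data. Nor does the clause unblind the assessors of EEG, EMG and kinematics. It would also go too far to say that learning of sham drives families to withdraw and so biases the results. These children are already excluded, and sham children are promised the active protocol at the end of the study.

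The wording is also loose. Coming straight after adverse effects, the guardian's questioning may have been meant as questioning about those effects. That is a fair reading of the intent, but nothing in the article restricts it, and a rule for breaking the blind should not depend on a charitable reading.

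Finally, the contacts are planned for adverse-effect follow-up. They are opportunities to ask, not expected unblindings, and repeated contacts with the same guardian are not independent. This stands: the percentages show sensitivity to an unknown rate and are not a forecast. The article already requires the reason for any exclusion to be recorded, so part of a log exists.

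**Conclusion.** The point holds as a fault in a stated rule. On the plain wording, a guardian's question is sufficient to reveal the arm, and disclosure removes the child from the results. The harm under the plan as written is a post-randomisation exclusion that families can trigger and that may be related to arm, together with loss of the sham blind for those families.

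Its size is unknown. If the chance per contact is 0.5% to 2% over 20 contacts, about 10% to 33% of children would be lost this way, against an allowance that tolerates 16.7% for all causes. These rates are assumptions with no source in the article. Whether the exclusions would in fact differ by arm is a risk and cannot be shown from the article. The change is worth making because the rule is explicit and the repair is cheap.

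**What to change.** In the Blinding section, delete the guardian's questioning as a trigger for unblinding. State in the protocol and the consent material that every family will be told the allocation after the 1-month assessment, and that staff will answer earlier questions without revealing the arm. Send guardians' concerns about adverse effects to the safety procedures already described under Data management and monitoring. Log each unblinding with its date, reason and arm.

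The cost is a short change to the protocol and consent form and a notification to the ethics committee. Some guardians will wait until follow-up ends to learn the allocation. That is a small burden, since offering the active protocol to sham children at the end of the study would in any case tend to reveal the arm then. This change does not settle how children unblinded through the adverse-effect trigger are analysed, which is a separate question.

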### Group allocation

The allocation of the participants will be concealed in sequentially numbered, sealed, opaque envelopes prepared prior to the study by a research assistant who will not be involved in the study. After the baseline measures have been collected, participants will be randomly assigned to the experimental or control group by the treating therapist, who will open the envelopes and read the contents. All outcomes will be measured by blinded assessors. All enrolled participants will receive a code to protect confidentiality before, during, and after the trial.

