#### Transcranial direct current stimulation (tDCS)

Stimulation will be administered using a tDCS device (DC-Stimulator NeuroConn, Germany) and two sponge (non-metallic) surface electrodes measuring 25 cm^2^ (5 × 5 cm) soaked in saline. The participants will be randomly allocated to two types of treatment: (1) active anodal tDCS and (2) sham tDCS. The anode will be positioned over F3 of the international 10-20 electroencephalogram system and the cathode will be positioned over the right deltoid muscle. This montage (Fig. 4) will enable the administration of anodal tDCS over the dorsolateral prefrontal cortex (DLPFC) while minimizing the effect of cathodal stimulation of the brain. The 1 mA current (current density: 0.029 mA/cm^2^) will be administered over the DLPFC for 20 min during upper limb training. The stimulator has a button that allows the operator to control the intensity of the current. Stimulation will be gradually increased to 1 mA at the beginning of the session and gradually decreased during the final 10 s of the session. Sham stimulation will consist of the same electrode montage and the stimulator will be turned on for 30 s, giving the child the initial sense of stimulation, but no current will be delivered for the remainder of the session. This is considered a valid control procedure in studies involving tDCS [40–48]. The participants will undergo a rehabilitation program while receiving tDCS. The rehabilitation program is based on the serial reaction-time task, which has been used extensively in upper limb studies. During the experiment, the participants will be seated on a chair in front of a touch screen monitor, head, and arms supported (ankle angle: ~ 110°; knee angle: ~ 150°; hip angle: ~ 120°). The participants will be instructed to avoid drinking coffee or consuming other stimulants on the day of the trial.

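### Children unblinded after randomisation are dropped from the results, so the active-versus-sham comparison rests on a set chosen by post-randomisation events

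*Protocol article*

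**What the plan says.** Under Blinding, disclosure to the guardian or participant takes place "if there is inconsistency in possible adverse effects and/or questioning on the part of the guardian". The consequence follows directly: "If this unblocking occurs, the individuals will be able to finish the protocol but will not compose the results of the study".

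Four other places bear on this rule:

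- **Group allocation.** "After the baseline measures have been collected, participants will be randomly assigned to the experimental or control group", so any later disclosure is a post-randomisation event. The same section states: "All outcomes will be measured by blinded assessors".
- **Exposure by arm.** In the sham arm "the stimulator will be switched on for only 30 s and then switched off" (Blinding). In the active arm the current "will be administered over the DLPFC for 20 min during upper limb training" (Transcranial direct current stimulation).
- **Adverse effects.** After each session the child is asked about symptoms "such as tingling, itching, burning sensation, headache, pain at the electrode site", among others. Under Data management and monitoring, guardians or children are also telephoned the day after each session, all adverse events are to be monitored and reported, and the reason for any exclusion is recorded.
- **Statistical analysis of results.** Phase 3 compares the two groups over time by repeated-measures ANOVA. No analysis set is named, and nothing elsewhere in the article brings the unblinded children back through an all-randomised analysis.

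**The concern.** This is a stated rule about who is analysed, not a detail left to an analysis plan. A later plan that analysed every randomised child would contradict it.

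Both triggers occur after allocation. The first concerns possible effects of the stimulation, and exposure to stimulation is what differs between the arms. The second is open-ended, with no criterion for which questions lead to disclosure and removal. If removal differs by arm and is related to outcome, the remaining active and sham children are no longer comparable, and the test of the hypothesis under Objective/hypotheses loses the protection of randomisation.

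There is a second consequence. Objective III is to determine the adverse effects of active stimulation. Read literally, the rule keeps out of the results children who were unblinded because of adverse effects.

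**Working it through.** **Is there a figure to reproduce?** No. The article gives no phase 3 sample size, effect size, SD or expected unblinding rate. The structural point is settled by reading; the arithmetic below only illustrates size.

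**Reading.**

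1. Allocation follows baseline, and disclosure follows allocation. Selection on disclosure is therefore selection after randomisation.
2. Disclosure is described only for the guardian or participant, outcome assessors are blinded, and the child may finish the protocol. The outcomes of these children can therefore still be collected by blinded assessors, so the rule discards obtainable data.
3. No other section restores these children to the analysis.

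**Illustration.** All inputs are assumptions: no true treatment effect; 26 children randomised per arm; unit SD among retained children; a fraction p_A of active and p_S of sham children excluded; excluded children scoring δ SD worse than retained children.

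In each arm, the mean of all children equals the retained mean minus p × δ. Deletion therefore raises the arm mean by p × δ, and

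bias = (p_A − p_S) × δ.

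The type I error comes from the noncentral t distribution, with retained numbers n_A = 26(1 − p_A) and n_S = 26(1 − p_S), n_A + n_S − 2 degrees of freedom, and noncentrality bias / √(1/n_A + 1/n_S).

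| Active / sham excluded | δ (SD) | Bias (SD) | Two-sided type I error |
|---|---|---|---|
| 10% / 5% | 0.5 | 0.05 × 0.5 = 0.025 | 5.1% |
| 10% / 5% | 1.0 | 0.05 × 1.0 = 0.05 | 5.3% |
| 20% / 5% | 0.5 | 0.15 × 0.5 = 0.075 | 5.7% |
| 20% / 5% | 1.0 | 0.15 × 1.0 = 0.15 | 7.8% |
| 30% / 5% | 1.0 | 0.25 × 1.0 = 0.25 | 12.4% |

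Worked line for 20% / 5%, δ = 1.0: n_A = 20.8, n_S = 24.7, √(1/20.8 + 1/24.7) = 0.298, noncentrality 0.15 / 0.298 = 0.50, which gives 7.8%.

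Reversing the rates (5% active, 20% sham) gives −0.075 to −0.15 SD, against active stimulation.

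**Cross-check by a different mechanism.** A simulation with 20 per arm (20,000 replicates, no true effect) excluded children with the lowest values of a latent score correlated with the outcome.

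- 20% versus 5% excluded, correlation 0.5: bias 0.12 SD, two-sided error 6.4%.
- Equal 20% exclusion in both arms, correlation 0.5: bias about 0, error 5.1%.
- 20% versus 5% excluded, correlation 0: bias about 0, error 4.9%.
- Everyone analysed as allocated: bias about 0, error 5.3%, which is nominal within simulation error.

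Bias therefore needs both conditions: exclusion that differs by arm, and exclusion that is related to outcome.

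**The case against.** The strongest reply is that the rule permits bias but does not establish it. Nothing in the article links skin sensations or a guardian's question to EEG activity, the primary outcome named for sizing under Study 2. The sham gives an initial sensation and is described as a valid control procedure, and the investigators expect no adverse events. If few children are unblinded, or the arms are balanced, the effect is negligible, as the 10% versus 5% rows show. The 20% and 30% rates and the 26 per arm have no anchor in the text. All of this stands, and it limits what can be said about size.

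Three stronger readings are tempting but not supported.

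- *Exclusion depends on perceived benefit.* The text says only that the guardian raises questions. Doubt about benefit is one possible reason, but it is an inference.
- *The bias favours active stimulation.* If guardians did ask because they saw no progress, and active stimulation worked, exclusions would fall more on sham and the sign would reverse.
- *The children with the worst tolerability disappear from the safety data.* The trigger is inconsistency in adverse effects, not severity. Symptoms are collected at every session, and all events must be monitored and reported. What is unclear is whether the results from which these children are removed include the safety results.

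The objection does not remove the defect. The analysed set is still defined by events after randomisation, and nothing in the article prevents the resulting bias.

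**Conclusion.** The exclusion rule is wrong as written and should be changed before phase 3 is analysed. That conclusion rests on the text alone and does not depend on any assumed rate.

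The size and direction of bias are unknown. Under the assumptions shown, they run from trivial (0.025 SD, 5.1% two-sided error) to material (0.25 SD, 12.4%), with the sign reversed if sham children are excluded more often. Bias is about zero if exclusions are balanced under the same mechanism or unrelated to outcome.

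The rule must also be reconciled with objective III and with the adverse event reporting under Data management and monitoring. When blinding should be broken is not judged here.

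**What to change.** Replace the exclusion sentence under Blinding with: *All randomised children are analysed, for efficacy and safety, in the group to which they were allocated, whether or not blinding was broken; unblindings are tabulated by arm and reason, and a sensitivity analysis excludes these children.*

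Add that blinded assessors continue to measure these children post-intervention and at one month.

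The cost is one protocol sentence, one short table and one sensitivity analysis. The children may already finish the protocol and reasons for exclusion are already recorded, so no extra visits are needed.
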